### **2.1 Study Overview**

The study will be conducted in the Matlab Health and Demographic Surveillance System (HDSS) field area of the International Centre for Diarrhoeal Disease Research, Bangladesh (ICDDR,B) to determine the population effectiveness of Rotarix in Bangladeshi children. Villages in both the Maternal and Child Health and Family Planning intervention area (hereafter referred to as the ICDDR,B service area) and the comparator Government service area will be included in this evaluation. We propose to introduce Rotarix into half of the villages of the Matlab HDSS. In villages randomized to receive the vaccine, all eligible children will be offered Rotarix during their first two Expanded Programme on Immunization (EPI) visits, as would routinely be done if Rotarix were included in the Bangladesh EPI schedule. If a child residing in a village assigned to Rotarix vaccine did not receive Rotarix during the first EPI visit, the child may still receive the Rotarix during subsequent EPI visits so long as the vaccine is given within age guidelines as defined by the Rotarix package insert. In villages randomized not to receive Rotarix, children will receive their EPI vaccinations exactly as they would have in the absence of this study. Administration of Rotarix will be conducted by regular EPI staff, but ICDDR,B study staff will be present to document informed consent and collect study-specific information. The Ministry of Health will be an active partner in this evaluation since they will be the agency which may follow up with any subsequent vaccine programme. Vaccination with Rotarix will be

recorded on the infant's immunization card which is normally used by the EPI programme, but also on a separate study-specific data collection form.

Rotarix vaccination started in the government service area villages in September 2008 (although was not fully operational until November 1 of that year) and in the ICDDR,B service area villages on April 1, 2009. The delayed start in the ICDDR,B service area was to allow for completion of follow-up in the RotaTeq individually-randomized trial which was carried out in the 67 villages of the ICDDR,B service area.

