## 2.5 Sample Size Considerations

### 2.5.1 Sample size calculations

The primary study endpoint will be admission for rotavirus gastroenteritis (see definitions, section 2.3.8). From 2003 to 2006 the average annual rotavirus admission rate to the Matlab Diarrhoeal Hospital among infants 0 to 11 months of age from the government comparison area was about 18.5 per 1000 and among infants 12 to 23 months of age it was 12.3 per 1000 (Table 3a); among infants 0 to 11 months of age from the intervention area it was 37.3 per 1000 and among infants 12 to 23 months of age it was 24.5 per 1000 (Table 3b). Because we will conduct surveillance among age-eligible infants continuously from study initiation, infants enrolled early will fall under longer surveillance while infants enrolled later will fall under brief surveillance (for example, only a few months). Additionally, because enrolment and surveillance for rotavirus diarrhoea will occur in the government comparison area and intervention area along different timelines, we used modeling to estimate a total study-period rotavirus diarrhoea hospitalization rate of 33 per 1000 infants (3.3%) (data not shown). With inclusion of infants admitted for rotavirus gastroenteritis at the Nayergaon and Kalirbazaar Community Treatment Centres, this rate may be slightly higher at 3.5%.

Because this is a cluster-randomized design, we must account for the intracluster (intra-village) correlation of acute rotavirus gastroenteritis. At the time of study planning, this value is not available for the study population. However, given the ubiquitous nature of rotavirus, we expected this value to be low (we assumed 0.02). Additionally, because we predefine clusters as villages for this study, we cannot set the cluster sizes to be equal; villages from the government comparison and intervention areas vary substantially in size (numbers of annual births). According to the timelines for enrolment for the 142 villages in from each area, the average cluster size is expected to be 65 with a coefficient of variation of cluster sizes is 0.96. Factoring in these values, along with the assumed intracluster correlation coefficient, into the calculation of the design effect for a cluster-randomized trial (Eldridge, 2006), we calculate a design effect of 3.48. Later estimations of the design effect based on rotavirus admission data for Matlab hospital place the design effect in the range of 2.9 to 4.5.

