|                                             | 
Three groups are definable for analysis of indirect effects.
 
Indirect Population 1
 
Those included: Infant and child residents of Matlab who are at least 20 weeks of age as of Apr 1, 2009 (ICDDR,B service area villages) or Nov 1, 2008 (Govt service area villages) or in-migrants to the study area who are between 20 weeks and 2 years of age during the study period. Treatment group assignment for these children will be determined by village of residency at the time that first allows them to be included in this population.
 
Follow-up period: Person-time will be counted from Apr 1, 2009 (ICDDR,B service area villages) or Nov 1, 2008 (Govt service area villages) or date of in-migration until two years of age (731 days) of age or March 31, 2011, whichever comes first.
 
Indirect Population 2
 
Those included: Infants who resided in Matlab between 6 and 20 weeks of age after Apr 1, 2009 (ICDDR,B service area) or after Nov 1, 2008 (Govt service area).
 
Follow-up period: Person-time will be counted from Apr 1, 2009 (ICDDR,B service area villages) or Nov 1, 2008 (Govt service area villages) or date of in-migration until receipt of OPV1, the child turns two years of age (731 days), or March 31, 2011, whichever comes first.
 
Indirect Population 3
 
Those included: All infants or children resident of the study area aged between 6 weeks and 2 years at some point during the study period.
 
Follow-up period: All person-time contributed during the study period. The analysis will account for receipt of vaccine (this will include any
 |

|  |                                                                                                |
|--|------------------------------------------------------------------------------------------------|
|  | indirect effects that also accrue to those who receive Rotarix, which is not 100% protective). |
|--|------------------------------------------------------------------------------------------------|

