### *Primary Aim*

*To evaluate the population (overall) (Halloran, et al., 1997) effectiveness of Rotarix in reducing rates of acute diarrhoea due to rotavirus, as detected by patients admitted to a study treatment facility, among all infants and young children from villages where Rotarix is introduced compared to among those from villages where Rotarix is not introduced.*

Main analysis, on Overall population: first episodes of rotavirus diarrhea. A Poisson regression with Pearson scale parameter (calculated at the village level) will be fit, offset with person-years of exposure, with a dummy covariate for village randomization arm status and a dummy covariate for villages in the Matlab service area (corresponding to the stratified randomization).

Note that this overall effectiveness is a function of vaccine efficacy and vaccine coverage. Since over 90% coverage is expected, this will not be much different from a total effects analysis. Also, if there are any indirect effects that act to reduce transmission, these may exert a differential effect over time, as it is not until near the end of the study period that the entire population of children under 2 years of age will be saturated with vaccine.

Additional analysis: same as main analysis, but including **all** episodes of rotavirus diarrhea, not just first episodes. The scale parameter at the randomization unit level also accounts for all within-child correlation, so the same analysis approach can be used.

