A detailed, yet “black box” analysis will use a Cox regression model with calendar timeline, with baseline hazard stratified by age at entry: 6wks-6 months, 6 months-1 year, 1yr-2yrs. The first step is to determine, for each village, for each day of the study, the time-varying proportion of infants and young children (6wks to 2 years) who have received at least 1 dose of OPV. Then, for each village, we find the 3 dates corresponding to when the village first achieves the proportions: 0.25, 0.50, 0.75. Thus, at any point in time, we can categorize each village into one of four immunization coverage categories: 0-24%, 25-49%, 50-74%, and 75-99%. There may be some misclassification in that a village may reach 27% one day and drop to 20% a month later, but these variations will be too difficult to track, and should not have much effect.

Crossing these four categories with whether a village is a Rotarix or control village yields 8 time-varying categories, which can be represented by 7 covariates:

$$R_{it}^{0-24}, R_{it}^{25-49}, R_{it}^{50-74}, R_{it}^{75+}, C_{it}^{25-49}, C_{it}^{50-74}, C_{it}^{75+}$$

where  $R$  and  $C$  correspond to Rotarix and control villages, respectively,  $i$  is for the  $i$ th infant, and  $t$  is for the infant's age in days. For example, if a given infant living in a Rotarix village is 87 days old on a given day, and on that day the village has already reached 25% coverage but not yet 50% coverage as defined above, then  $R_{it}^{25-49} = 1$  and the other 7 covariates are coded as 0.

Note the reference category is 0-24% coverage in a control village. In addition, we will track the immunization status of each infant with the variable  $Vac_{it}$  which starts as 0 and becomes 1 upon first OPV. This variable is not of much interest—its coefficient will estimate any protective effect due to selection for vaccination. Crossing this term with village type of residence, denoted by  $X_i$  ( $=1$  for Rotarix,  $0$  for control) yields an interaction term that indicates the individual-level protection afforded by Rotarix. Putting this all together into a specification of the hazard function, we get:

$$\lambda_i(t) = \lambda_0(t) \exp(\beta_1 Vac_{it} + \beta_2 X_i Vac_{it} + \beta_3 R_{it}^{0-24} + \beta_4 R_{it}^{25-49} + \beta_5 R_{it}^{50-74} + \beta_6 R_{it}^{75+} + \beta_7 C_{it}^{25-49} + \beta_8 C_{it}^{50-74} + \beta_9 C_{it}^{75+})$$

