where  $\lambda_0(t)$  is the unspecified baseline hazard function.  $X_i$  does not appear by itself because there is no expected effect of whether a child lives in a Rotarix or control village *per se*, as that was determined through randomization.

The indirect effects at any given level of coverage are estimated by taking the difference of the relevant covariates. For example,  $\exp(\beta_6 - \beta_9)$  gives the relative hazard of those in a highly Rotarix-immunized village compared to those in a highly OPV-only immunized village. Note there will not be a great deal of power for these comparisons, however.

It will also be advisable to add two time-varying dummy variables to track the three main seasons (see the seasonality discussion below).

The best way to analyze these data is to use a gamma frailty model that assigns a random intercept term to each village to account for within-village correlation. Stata has a function for this, although it will take some careful work to split up each child's observation time into a number of intervals to account for all the time-varying covariates. It may also be possible to use the SAS PROC SURVEYPHREG to estimate a robust variance to account for the correlation. The advantage to this approach is that SAS allows for continuously-varying time-varying covariates that are relatively easily coded. If this specification in SAS, that will be the preferred approach for analysis.

*3. To evaluate the direct effectiveness of Rotarix in reducing rates of acute diarrhoea due to rotavirus, as detected by patients admitted to a treatment facility, among vaccinated infants and young children from villages where Rotarix is introduced compared to unvaccinated infants and young children from villages where Rotarix is introduced.*

This direct effect is best estimated by  $\beta_2$  in the above model, which is the remaining effect of Rotarix after accounting for the indirect effects. This will be run for the mITT population.

A second estimate will be provided by applying a Cox model to the Direct effect population (i.e. the mITT population only in Rotarix villages), with a time-varying covariate for receipt of first dose of Rotarix.

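### The Cox model for indirect and direct effects omits the service-area term that the Poisson models carry; adding it is a minor, nearly free improvement

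*SAP*

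**What the plan says.** SAP section 3.5, Secondary Aim 2(c), says the analysis "will use a Cox regression model with calendar timeline, with baseline hazard stratified by age at entry". The hazard contains vaccination status, its interaction with village arm, and seven indicators that cross arm with four bands of village OPV coverage. The reference is a control village at 0-24%. The only further covariates are seasonal: "It will also be advisable to add two time-varying dummy variables to track the three main seasons". Within-village correlation is handled by a village gamma frailty, called the best way, or by a robust variance in SAS, of which the SAP says: "If this specification in SAS, that will be the preferred approach for analysis". Neither version has an area term or stratum.

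Indirect effects are differences between arms within a band, for example exp(β6 − β9). The direct effect (Secondary Aim 3) is β2. A second direct estimate comes from a Cox model in Rotarix villages only, with a time-varying covariate for the first Rotarix dose. Section 3.6(b) uses the same kind of Cox model for total effects.

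The Poisson model for the primary aim, by contrast, includes "a dummy covariate for villages in the Matlab service area (corresponding to the stratified randomization"), and the main total-effectiveness model has the same dummy.

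**The concern.** Three facts in the SAP make area a strong candidate covariate. Villages in the two areas were randomised separately (section 2.2). The areas enter at different times: Rotarix began "in the ICDDR,B service area villages on April 1, 2009", against an effective start of November 1, 2008 in the government area, and section 2.5.1 notes that "surveillance for rotavirus diarrhoea will occur in the government comparison area and intervention area along different timelines". The background rates also differ: "among infants 0 to 11 months of age from the intervention area it was 37.3 per 1000", about twice the government-area figure.

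A model that leaves out the factor by which the trial was stratified gives up precision and lets chance differences in area mix into the arm comparison. Where a comparison is not randomised, as in the second direct estimate, area can confound it outright. On a calendar timeline with staggered starts, a time-varying coverage band can also come to stand in for area.

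**Working it through.** **Inputs from the SAP**
- Villages: 75 government, 67 ICDDR,B (section 2.2). Village-size coefficient of variation 0.96 (section 2.5.1).
- Admission rates per 1000 per year, Matlab Diarrhoeal Hospital, 2003-2006 (section 2.5.1): government 18.5 (0-11 months) and 12.3 (12-23 months); ICDDR,B 37.3 and 24.5. Ratios: 37.3/18.5 = 2.02 and 24.5/12.3 = 1.99.
- Start dates (section 3.2, Indirect Population 1): "Person-time will be counted from Apr 1, 2009 (ICDDR,B service area villages) or Nov 1, 2008 (Govt service area villages"). The gap is 30 + 31 + 31 + 28 + 31 = 151 days.

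The SAP gives no figure for the Cox model. Its sample-size figures do reproduce: design effect 1 + ((0.96² + 1) × 65 − 1) × 0.02 = 3.48; 77 × 3.48 = 268 admissions; 268/(0.035 × 0.75) = 10,210 infants.

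**Assumptions not in the SAP**
- Coverage is counted from each area's launch.
- The individual vaccine hazard ratio is 0.5, and there is no true indirect effect.
- The area hazard ratio is about 2, from the rates above.

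The Cox model was fitted as a Poisson model with calendar-month baseline effects, its piecewise equivalent.

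**1. The named contrasts.** Fitted to expected counts, exp(β6 − β9) is 1.01 without an area term and 1.00 with one (truth 1). exp(β2) is 0.50 both ways (truth 0.50).

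**2. Chance imbalance and precision.** Over repeated random allocations with village sizes varying as stated, the 95% range of exp(β6 − β9) is about 0.93 to 1.07 without area and 1.00 to 1.01 with it. In 200 simulated trials (area rates 15.4 and 31 per 1000 per year, between-village variance 0.3), the mean robust standard error falls from 0.301 to 0.289 when area is added. The variance ratio is (0.289/0.301)² = 0.92, about 8% less. For scale, a standard error of 0.301 gives a 95% interval of exp(±1.96 × 0.301), a factor of about 1.8 either way. In 12 further data sets the actual spread of the log contrast was 0.254 without area and 0.253 with it, so the gain is in the reported standard error and is modest.

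**3. Second direct estimate (Rotarix villages only).** Let coverage be g in the government area and c in the ICDDR,B area, with equal person-time and an area hazard ratio of 2. The apparent hazard ratio is

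0.5 × [(g + 2c)/(g + c)] ÷ [((1 − g) + 2(1 − c))/((1 − g) + (1 − c))].

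- g = c = 0.90: 0.5 × 1.500/1.500 = 0.50
- g = 0.85, c = 0.95: 0.5 × 1.528/1.250 = 0.61
- g = 0.95, c = 0.85: 0.5 × 1.472/1.750 = 0.42
- g = 0.88, c = 0.92: 0.54; reversed: 0.465

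The SAP expects coverage above 90% but gives no figure by area.

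**4. Separate band coefficients.** If coverage builds from each launch, government villages run about five months ahead. Near each threshold the two areas then sit in different bands on the same date, and each step up absorbs roughly the twofold rate difference. Control-village hazard ratios against the 0-24% control band (truth 1), fitted to expected counts:

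| Band | No area term | Area term |
|---|---|---|
| 25-49% | 0.50 | 0.94 |
| 50-74% | 0.26 | 0.90 |
| 75%+ | 0.14 | 0.88 |

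The 200 trials gave 0.52, 0.27 and 0.15 without area. The shortfall from 1 that remains with an area term is not due to area: it is much the same (0.875 at 75%+) when the area hazard ratio is set to 1. In the 12 data sets, gamma frailty without area gave 0.17 for the top band, so a village intercept does not stand in for the area term.

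**5. Dummy or stratum.** In 40 simulated trials the median standard error of β9 was 0.48 with no area term, 0.55 with a dummy and 0.70 with area strata. For β6 − β9 it was 0.304, 0.290 and 0.290.

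**The case against.** The strongest reply is that the SAP does not use the coefficients that go wrong. It defines an indirect effect as a difference between arms at the same coverage level, and a shift common to both arms cancels in that difference. Randomisation within area makes the area mix alike in both arms on average, and β2 is unaffected. The SAP also calls this analysis a black box and warns of low power. All of this stands.

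A reader might infer that the plan would report false herd protection, citing control-village hazard ratios as low as 0.14. The documents do not support that. The SAP gives no effect interpretation to a band coefficient alone or to a comparison across bands. The mechanism also needs coverage to be counted from launch. Section 3.5 defines coverage as the share with at least one OPV dose and gives no launch date. Read literally, with routine OPV and coverage above 90%, most villages could start in the top band and the bands would hardly vary. The three threshold dates, and the remark under the primary aim that saturation comes only late, point towards the launch-based reading, but the text does not settle it.

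Two further limits apply. Indirect Population 3 refers only to the study period, so the staggered start is implied for this model, not stated. The twofold ratio comes from one hospital before the study, which adds treatment-centre cases.

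**Conclusion.** The omission is real and inconsistent with the Poisson models, but its effect on the named estimates is small. The within-band indirect contrast and β2 are essentially unbiased on average. What is lost on the indirect contrast is avoidable imbalance of about 7% either way and about 8% in estimated variance, both small against an interval spanning a factor of about 1.8 either way.

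The second direct estimate is the most exposed, because vaccination within Rotarix villages is not randomised. The bias depends wholly on a coverage difference between areas that the SAP does not give: none if equal, and 0.42 or 0.61 for a true 0.50 at the assumed 85%/95%. The confounding of separate band coefficients is large but conditional on the launch-based definition of coverage, and it matters only if bands are compared with one another.

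This is a minor point on secondary and exploratory analyses: a free improvement, not a flaw in the plan's main conclusions.

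**What to change.** Add the service-area dummy already defined for the Poisson models to three places: the hazard in Secondary Aim 2(c), the second direct-effect Cox model under Secondary Aim 3, and the Cox model in section 3.6(b). Do so in both the robust-variance and the frailty versions. The severity analyses in Secondary Aim 4 then inherit it. Stratifying the baseline hazard by area is an acceptable alternative; it may cost precision on individual band coefficients, though not on β6 − β9.

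State that indirect effects are read only as Rotarix-minus-control differences within a coverage band, never across bands. Say also whether coverage is counted from each area's launch.

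The cost is one covariate and a few sentences. No new data are needed.

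### The Secondary Aim 2(c) Cox model counts any OPV dose, including doses given before Rotarix was introduced, so its coverage categories do not track Rotarix coverage

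*SAP*

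**What the plan says.** SAP section 3.5, Secondary Aim 2(c), builds a Cox model on two OPV variables.

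- **Village coverage.** For each village and study day it takes "the time-varying proportion of infants and young children (6wks to 2 years) who have received at least 1 dose of OPV". Then "we find the 3 dates corresponding to when the village first achieves the proportions: 0.25, 0.50, 0.75", which gives four categories per arm. "Note the reference category is 0-24% coverage in a control village".
- **Individual status.** Vac is a variable "which starts as 0 and becomes 1 upon first OPV". Crossing it with village arm "yields an interaction term that indicates the individual-level protection afforded by Rotarix" (β2).

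The population is Indirect Population 3 of section 3.2: "All infants or children resident of the study area aged between 6 weeks and 2 years at some point during the study period". It therefore includes the older children who also form part of Indirect Population 1, described as "Infant and child residents of Matlab who are at least 20 weeks of age as of Apr 1, 2009" (Nov 1, 2008 in the Government area).

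The SAP reads exp(β6-β9) as the hazard in a village with high Rotarix immunization relative to one with high OPV-only immunization. For the direct effect (Secondary Aim 3) it runs the same model on the mITT population.

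Elsewhere, when section 3.2 uses OPV1 as the marker of an opportunity to receive Rotarix (overall secondary population, first-priority mITT population), it excludes the birth dose and requires the dose to fall after the area's introduction date.

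**The concern.** OPV is routine EPI vaccination that was given before Rotarix. Read as written, a child of 18 months on the first study day who had OPV in infancy counts as covered, although no Rotarix had yet been given in that village. This conflicts with the rest of the model. The SAP expects villages to pass 25%, 50% and 75% during follow-up, and under the Primary Aim it expects full vaccine saturation only late ("it is not until near the end of the study period that the entire population of children under 2 years of age"). Both hold only if doses are counted from introduction.

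Two things are at stake. The coverage categories, which carry the indirect effect, may hardly vary over time. And β2 in the Indirect Population 3 fit may mix children who could have had Rotarix with children who were too old for it. Secondary Aim 4 repeats the analyses for severe disease, so the defect repeats there.

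**Working it through.** The SAP gives no figure that depends on these definitions, so there is none to reproduce. The check asks what the definitions imply.

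**Inputs from the SAP.** Ages 6 weeks to 731 days (104.43 weeks), a span W = 98.43 weeks. Introduction Nov 1, 2008 (Government) and Apr 1, 2009 (ICDDR,B), with an end date of Mar 31, 2011, so T = 125.7 and 104.1 weeks. Vaccination window 6-20 weeks. Coverage expected during the trial: over 90%. Assumed effectiveness: 50%. Age-specific rates for 0-11 and 12-23 months per 1000: 18.5 and 12.3 (Government), 37.3 and 24.5 (ICDDR,B). About 11,650 births in 142 villages, which gives about 70 children aged 6 weeks to 2 years per average village.

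**Assumptions.** Steady births and uniform ages. Pre-study OPV1 uptake c is not in the SAP and is varied. OPV1 is given all at 6 weeks, evenly over 6-20 weeks, or all at 20 weeks. Birth doses are ignored; counting them would raise coverage.

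**1. Day-1 coverage as written.** Coverage = c × (share of the age group past OPV1). That share is 1 (all at 6 weeks), 1 - 7/98.43 = 0.929 (even), or 84.43/98.43 = 0.858 (all at 20 weeks).

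| c | all at 20 weeks | even | all at 6 weeks |
|---|---|---|---|
| 80% | 69% | 74% | 80% |
| 85% | 73% | 79% | 85% |
| 90% | 77% | 84% | 90% |

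Actual Rotarix coverage on that day is 0%.

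**2. Which cells are empty.** Treating children as independent (binomial) with coverage 0.836, a 70-child village starts below 75% with probability about 3% and below 50% with probability near 0. For a 10-child village these are 22% and 0.2%. At the lowest corner of the table (0.686), a 70-child village starts below 75% with probability about 88% and below 50% with probability about 0.04%; a 10-child village starts below 50% with probability about 6% and below 25% with about 0.2%. So the 0-24% and 25-49% cells are practically empty throughout, but the 50-74% cell need not be.

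**3. Children aged 20 weeks or more at introduction.** Share of the age group on day 1: 84.43/98.43 = 86%. Their person-time until age 2, per child present on day 1: 84.43²/(2 × 98.43) = 36.21 weeks. Share of all person-time: 36.21/125.7 = 29% (Government) and 36.21/104.1 = 35% (ICDDR,B).

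**4. Share of time coded X·Vac = 1** (even timing; c cancels): 36.21/(125.7 × 0.929) = 31% and 36.21/(104.1 × 0.929) = 37%. Weighted by the SAP's age-specific rates: 27% and 33%.

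**5. Crude dilution of β2.** Apparent effect = 1 - [s + (1 - s) × 0.5]. With s = 0.310 and 0.374 this is 34% and 31%; with the rate-weighted 0.274 and 0.329 it is 36% and 34%. The range is 31-36% against a true 50%. It ignores the calendar timeline and the stratification by age at entry.

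**6. Counting only OPV1 given from introduction.** Coverage starts at 0% and, for the first 84 weeks, equals c × (weeks since introduction)/98.43. At c = 90% it reaches 25%, 50% and 75% at about weeks 27, 55 and 82, inside both study periods. At lower uptake 75% may not be reached: with c = 80% and even timing the ceiling is 0.80 × 0.929 = 74%.

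**The case against.** - **The direct effect is not diluted.** A reader might infer that the planned direct-effectiveness estimate falls from 50% to the figures above. It does not. That β2 is run on the mITT population, and both versions of it in section 3.2 tie inclusion to ages 6-20 weeks after introduction, so the older children are out. The second direct estimate uses receipt of the first Rotarix dose. This objection stands; only the coverage-category defect carries over to the mITT run.
- **Saturation on day 1 is not documented.** The expectation of over 90% concerns the trial period, and at 80-85% uptake some villages would start in the 50-74% band. This stands, so it cannot be said that every village begins at 75% or that the 50-74% cell is empty. The near-emptiness of the two lowest bands does survive.
- **The contrast is not void.** One might infer that exp(β6-β9) would not measure Rotarix coverage at all. The later months in the top category do have high Rotarix coverage, so the contrast is an average over near-zero to full coverage: blurred, not meaningless.
- **The text can be read as intended.** Vac starting at 0 could mean that children vaccinated before entry stay at 0, and the surrounding text points to doses after introduction. That is possible, but the wording does not settle it for Vac, and the coverage definition has no such opening.
- **It is a low-power secondary analysis.** The SAP itself says so. This limits the consequence but does not make the definition right.

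**Conclusion.** The concern holds for the 2(c) Cox model as written. Coverage and Vac lack the introduction-date limit and birth-dose exclusion that section 3.2 applies to OPV1. If pre-study OPV uptake was 80-90%, day-1 coverage is about 69-90%, the reference and 25-49% cells are practically empty, and the top Rotarix category includes early months with almost no Rotarix. Because a village keeps the category it first reaches, exp(β6-β9) cannot be read as the effect of living in a village with high Rotarix coverage.

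In the Indirect Population 3 fit, if earlier OPV sets Vac to 1, about 31-37% of the time coded X·Vac = 1 belongs to children too old for Rotarix at introduction. The fall from 50% to 31-36% is illustrative only.

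Unaffected: the primary and total-effectiveness Poisson analyses, the Poisson analyses of Indirect Populations 1 and 2, and the second direct estimate. The results rest on steady births, uniform ages and the assumed uptake range.

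**What to change.** In Secondary Aim 2(c), for both arms:

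1. Define the coverage numerator, and the Vac term used in X·Vac, by OPV1 (not the birth dose) received on or after the area's introduction date and within the SAP's 6-20-week window. A date filter alone is not enough: a child already past 20 weeks at introduction who has a late first OPV would still be coded as Rotarix-protected.
2. Keep all resident children aged 6 weeks to 2 years in the denominator.
3. Carry a separate main-effect indicator for any OPV1, earlier doses included. Otherwise children with earlier OPV would be pooled with the unvaccinated, and β1 would lose its stated meaning as a selection effect.

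The cost is a few sentences in the SAP, a date and age filter, and one more covariate. The SAP already needs OPV dates for the section 3.2 populations. Section 1 says the plan is being finalized without knowledge of results by arm, so the change can be made now without looking post hoc.
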